**Figure 1 fig1:**
[figure not shown]
Flowchart of the study design.

### Interventions

2.5

The intervention will be delivered over an eight-week period by members of the research team, including qualified physiotherapists and physical activity and sports science professionals. It will combine exercise and health education in a hybrid format (face-to-face and app-based), consisting of eight on-site educational workshops and a structured app-based exercise program.

#### Face-to-face workshops

2.5.1

Participants will attend eight structured group workshops, delivered one per week, during working hours at the company’s facilities. To optimize accessibility and participation, sessions will be scheduled separately for each work shift (morning, afternoon, and night).

An initial introductory workshop will be delivered before starting the exercise program to ensure safe participation. It will include instruction on the use of exercise materials, guidance on adjusting exercise intensity, and basic guidance on muscle activation and correct execution of basic exercises.

Workshops will follow structured educational programs using standardized materials to ensure consistency across groups. The content will address:

Pain mechanisms and coping strategies, with emphasis on self-efficacy.Principles of strength and aerobic exercise.Mobility training.Stress management and relaxation techniques.Active rest strategies during the working shift.Sleep hygiene and healthy lifestyle habits.Review sessions aimed to clarify doubts and reinforce learning through group discussion.

During these sessions, participants will also receive guidance on the digital exercise component and may ask questions about prescribed exercises.

#### App-based exercise program

2.5.2

Participants will complete two weekly exercise sessions via the RehBody digital platform, a mobile-based software that enables remote prescription, delivery and monitoring of exercise programs through video demonstrations, written instructions and automated session tracking. RehBody is a paid platform; however, for the purposes of this study, access will be provided free of charge to all participants for the duration of the intervention as part of their participation in the research. Participants will receive individual login credentials and instructions on how to access and use the platform during the initial workshop.

Individualized programs will be assigned and updated based on baseline assessments, and investigators will monitor adherence and progression through the platform’s control panel. Participants will be able to access the program via smartphone or computer. To support engagement, the platform will also include visual progress tracking and structured exercise logging. Furthermore, participants will be able to contact the research team through the platform to receive feedback if they have doubts about exercise execution or experience discomfort.

The program will be designed to promote general mobility, scapular and spinal stability, and upper- and lower-limb strength, with a particular focus on preventing injuries and strengthening the joints most affected by the company’s work tasks, including the shoulders, wrists, elbows, and hips. Each session will follow a structured progression, beginning with a warm-up of mobility exercises and core activation, and continuing with a main phase targeting key muscle groups. Exercise intensity and complexity will progressively increase, from simple bilateral movements to complex unilateral and multi-joint tasks. The volume and complexity of exercises will be adjusted according to participants’ perceived difficulty and tolerance, and any repetitions that cause excessive discomfort will be modified to maintain therapeutic benefit while minimizing symptom exacerbation. The structure and progression of the exercise program are detailed in Table 1.

**Table 1 tab1:** Structure and progression of the 8-week exercise program.

Phase	Weeks	Main objective	Target region	Exercise characteristics	Volume and intensity	Progression criteria (App-based)
Phase 1: adaptation	1–2	Restore motor control and neuromuscular adaptation	Deep trunk stabilizers, scapular stabilizers, hip stabilizers	Low-load, bilateral, predominantly single-joint exercises; low coordination demand	2–3 sets; 10–12 reps RPE 3–4	≥80% session completion; pain ≤3/10; RPE ≤ 4; No symptom worsening within 24 h
Phase 2: load introduction	3–4	Develop basic strength and joint stability	Shoulder complex; wrist stabilizers; lumbopelvic region	Bilateral multi-joint exercises; increased ROM and core engagement	2–3 sets; 12–15 reps; RPE 4–5	≥80% adherence; Average RPE ≤ 5; No adverse events
Phase 3: dynamic stability and unilateral control	5–6	Enhance dynamic stability and unilateral neuromuscular control	Rotator cuff, scapulothoracic musculature, hip abductors and extensors	Unilateral multi-joint exercises; increased balance and coordination demands	3 sets; 8–12 reps; RPE 5–6	≥80% Adherence; RPE 5–6 without excessive fatigue; Positive tolerance feedback
Phase 4: functional integration and movement efficiency	7–8	Integrate strength into functional movement patterns	Upper limb–trunk–hip kinetic chain	Functional, task-oriented multi-joint exercises; higher coordination, control, and movement efficiency demands	3 sets; 8–10 reps; RPE 6–7	≥80% adherence; RPE ≤ 7; Self-reported readiness to progress

All participants will receive an exercise kit designed to facilitate the completion of home-based sessions, including elastic bands of different resistance levels, an exercise mat, a foam roller, and massage balls.

Adherence to the intervention will be monitored using attendance records for face-to-face workshops and usage data from the RehBody application. Participants will be considered adherent if they attend at least 80% of the planned sessions. This adherence threshold will be used to define the per-protocol sample for the primary analysis.

TIDieR alignment: The intervention description follows the TIDieR checklist, specifying what, who, how, where, when, how much, and individualization/progression.

### Outcomes

2.6

#### Sociodemographic data

2.6.1

Sociodemographic data and work-related characteristics will be collected before the intervention using an *ad hoc* questionnaire, including age, sex, job seniority, and work shift. This data will be used to describe and support the interpretation of the study findings.

#### Primary outcome

2.6.2

*Pain intensity:* Pain intensity will be measured using the Numeric Rating Scale (NRS), an 11-point validated self-reported measure widely used in musculoskeletal and occupational health research. Participants will be asked to rate their average musculoskeletal pain on a scale ranging from 0 (no pain) to 10 (worst imaginable pain) during face-to-face assessment sessions.

The NRS has demonstrated good reliability, validity, and responsiveness to change in musculoskeletal populations. Scores are commonly interpreted as: mild pain (1–3), moderate pain (4–6), and severe pain (7–10) (17).

The MCD for the NRS in musculoskeletal pain has been estimated at 1.5–2 points, which will be used to interpret the clinical relevance of pre–post changes (18). The primary outcome will be the change in NRS scores from baseline to post-intervention.

### Secondary outcomes

2.7

*Musculoskeletal symptoms:* Musculoskeletal symptoms will be assessed using the Standardized Nordic Musculoskeletal Questionnaire (NMQ) developed by Kuorinka et al. (19) This questionnaire assesses the presence of pain or discomfort in nine body regions (neck shoulder, elbows, wrists/hands, upper-back, hips/thighs, knees and ankles/feet). Participants will indicate whether they have experienced musculoskeletal symptoms in each body region during the preceding 12 months and the preceding 7 days, and whether these symptoms have resulted in limitations in normal work activities.

The NMQ will allow the assessment of the prevalence, anatomical distribution, and work-related functional impact of musculoskeletal symptoms in this occupational population, as well as their changes following the intervention. The Spanish version of the NMQ has demonstrated adequate reliability and content validity, supporting its use in Spanish-speaking working populations (20, 21).

*Muscle strength:* Upper-limb muscle strength will be assessed using a handgrip dynamometer (Takei Grip-D dynamometer) to measure maximal handgrip force (kg), following standardized testing procedures. Participants will perform the test in a seated position with the elbow flexed at 90°, and the highest value of three trials will be recorded.

Handgrip strength is a reliable and valid indicator of general muscle strength and functional health, and it has been extensively used in occupational and clinical populations (22, 23). Reference values adjusted for age and sex will be used for interpretation. The test demonstrates excellent test–retest reliability and concurrent validity, with high intraclass correlation coefficients reported across populations.

*Functional Capacity:* Functional capacity will be evaluated using the 30-s Sit-to-Stand test which quantifies the number of complete sit-to-stand repetitions performed within 30 s. This measure serves as an indicator of lower-limb strength and functional ability associated with everyday and work-related tasks. The 30s STS test is a commonly used, valid and reliable measure of lower extremity strength and functional performance in populations with chronic musculoskeletal pain and working-age adults.

*Physical activity level:* Physical activity level will be assessed using the short form of the International Physical Activity Questionnaire (IPAQ-SF). This self-administered questionnaire records the frequency and duration of walking, moderate-intensity, and vigorous physical activity performed during the previous seven days (24).

This outcome will be expressed in MET minutes per week and categorized as low, moderate, or high according to established scoring guidelines. The IPAQ-SF has demonstrated acceptable reliability and validity for population-based studies and has been validated in Spanish-speaking populations (25, 26).

*Work ability:* Work ability will be evaluated using the Work Ability Index (WAI), a multidimensional self-administered questionnaire that evaluates perceived work ability in relation to job demands, health status, and mental resources. The total score ranges from 7 to 49 points, with higher scores reflecting better perceived work ability, and is classified into four categories: poor (7–27), moderate (28–36), good (37–43), and excellent (44–49) (27). The WAI has been widely used in occupational health research and has demonstrated good psychometric properties, including validation in Spanish working populations.

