In addition to clinical and work-related outcomes, selected process indicators will be descriptively reported to contextualize feasibility aspects of the intervention in this occupational setting. These will include recruitment rate, attendance to face-to-face workshops, adherence to the app-based exercise sessions, and retention at follow-up. These indicators will be intended to inform interpretation of the results and guide future-controlled studies.

All outcome variables and their corresponding assessment time points are detailed in Table 2.

**Table 2 tab2:** Outcome measures.

Outcome measure	Baseline (T0)	Post-intervention 8 weeks (T1)	Follow-up 12 weeks (T2)
Primary outcome			
Pain intensity (NRS)	✓	✓	✓
Secondary outcomes			
Musculoskeletal symptoms (NMQ)	✓	✓	✓
Upper-limb muscle strength (Handgrip dynamometry)	✓	✓	✓
Functional capacity (30-s Sit-to-Stand test)	✓	✓	✓
Physical activity level (IPAQ-SF)	✓	✓	✓
Work ability (WAI)	✓	✓	✓
Sleep quality (PSQI)	✓	✓	✓
Depression, anxiety and stress (DASS-21)	✓	✓	✓
Health-related quality of life (EQ-5D-5L)	✓	✓	✓
Work productivity and absenteeism (WPAI)	✓	✓	✓
Sociodemographic and work-related variables	✓	—	—
Process/feasibility indicators			
Recruitment rate	—	✓	—
Workshop attendance	—	✓	—
Adherence to app-based exercise sessions	—	✓	✓
Retention at follow-up	—	—	✓

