### Data collection procedure

2.8

Baseline assessments will be conducted face-to-face at the company’s facilities. Questionnaire-based outcomes will be completed on paper under the supervision of a member of the research team, while physical tests will be administered by qualified professionals following standardized protocols.

All outcome measures, except for baseline sociodemographic data, will be reassessed immediately after completion of the intervention and at a one-month follow-up, using identical assessment protocols, time schedules and, where possible, by the same assessor.

All collected data will be anonymized and coded using a unique identification number assigned to each participant. Personal identifying information will be stored separately from research data and will be accessible only to the principal investigator. Paper-based questionnaires will be kept in locked cabinets at Universidad San Jorge, and electronic data will be entered into a password-protected database hosted on secure institutional servers compliant with European data protection regulations (GDPR and Spanish Organic Law 3/2018). Data entry will be double-checked to minimize transcription errors, and range and consistency checks will be performed prior to statistical analysis. Data will be retained for 5 years following study completion and then securely destroyed.

Figure 2 presents the study timeline and key procedural details.

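### The NMQ 12-month symptom item is repeated at 8 and 12 weeks as part of a change outcome, although 85% and 77% of its recall window precede the programme; the 7-day item should carry the change analysis

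*Protocol article*

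**What the plan says.** Section 2.7 (Secondary outcomes) describes the NMQ as a set of questions for each body region: "Participants will indicate whether they have experienced musculoskeletal symptoms in each body region during the preceding 12 months and the preceding 7 days". It adds a question on whether the symptoms limited normal work and gives that question no recall period of its own. The section says the NMQ will measure prevalence, distribution and work impact, "as well as their changes following the intervention". It does not separate the 12-month item from the 7-day item for that purpose.

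Table 2 schedules the NMQ at T0, at T1 (8 weeks) and at T2 (12 weeks). Section 2.8 (Data collection procedure) confirms this: "All outcome measures, except for baseline sociodemographic data, will be reassessed immediately after completion of the intervention and at a one-month follow-up". The same section has the form and procedure stay the same from visit to visit, "using identical assessment protocols". Section 2.5 sets the programme length at eight weeks. Nothing in the article restricts the 12-month item to baseline or names the 7-day item as the measure of change.

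**The concern.** A question that looks back 12 months is being asked twice within three months of baseline, and its answers are covered by a general statement that the NMQ will show change. Most of what the worker reports at T1 and T2 happened before the first session. A worker who has recovered completely will usually have to give the same answer as at baseline.

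If the plan is followed as written, the change in 12-month prevalence will be close to nil almost regardless of what the programme does, and a small fall will be hard to interpret. The design has a single arm, so no comparison group shows how much movement would occur anyway. A reader could take a flat result as absence of benefit, or a small fall as benefit, and neither reading would be justified.

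**Working it through.** The article gives no figure for this point, so there is nothing to reproduce. The check is arithmetic on the stated windows and visits.

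**Inputs**
- Recall windows: 12 months, taken as 52 weeks, and 7 days (section 2.7).
- Weeks from programme start to visit: 8 at T1 and 12 at T2 (section 2.5, Table 2).

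**Share of the 12-month window before the programme** = (52 − weeks since start) / 52
- T1: (52 − 8)/52 = 44/52 = 84.6%
- T2: (52 − 12)/52 = 40/52 = 76.9%

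For the 7-day item the share is 0% at both visits.

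**What follows without further assumptions, given accurate recall.** A region that was symptomatic at any time in the last 44 weeks before the programme must be answered yes at T1. For T2 the same holds for the last 40 weeks. A truthful switch from yes to no requires symptoms confined to the oldest 8 (T1) or 12 (T2) weeks of the baseline window and none since.

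**Illustration of size.** Assume that each region is symptomatic in any given week with probability p, independently across weeks. This is a simplification and p is not in the documents, so a range is shown. Baseline 12-month prevalence is 1 − (1 − p)^52. If every symptom stops on the first day of the programme, it becomes 1 − (1 − p)^44 at T1 and 1 − (1 − p)^40 at T2.

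| p | Baseline and no effect | T1, total cure | T2, total cure |
|---|---|---|---|
| 0.02 | 65.0% | 58.9% | 55.4% |
| 0.05 | 93.1% | 89.5% | 87.1% |
| 0.10 | 99.6% | 99.0% | 98.5% |

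The 7-day prevalence would fall to zero in every row. With the target of 33 participants (section 2.9), the T1 fall in the first row is 33 × (0.650 − 0.589) = about 2 workers per region under a perfect cure.

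**Where the yes-to-no switches come from**, for p = 0.02 at T1. The probability that a region is symptomatic in the oldest 8 weeks is 1 − 0.98^8 = 0.149.
- No effect: the later 44 weeks and the 8 programme weeks must all be clear, so 0.98^52 × 0.149 = 0.350 × 0.149 = 5.2%.
- Total cure: only the later 44 weeks need to be clear, so 0.98^44 × 0.149 = 0.411 × 0.149 = 6.1%.

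In this illustration, most yes-to-no switches would occur with no programme effect at all. They are old episodes leaving the window.

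**The case against.** Four points can be made for the plan.

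**The item is not completely fixed.** A reader might infer that 12-month prevalence can only stay level or rise, or that any fall must be recall error. Neither is right. The window rolls forward, so episodes confined to its oldest weeks drop out truthfully, and the table shows falls under perfect recall. Preventing new or recurrent episodes also has a small influence. This objection stands, and the claim is limited to low sensitivity.

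**The NMQ as a whole can still show change.** The 7-day item lies wholly after the programme start at both follow-up visits and is already collected. The article does not single out the 12-month item as the change measure. It would be wrong to conclude that the NMQ outcome is unusable. This also stands.

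**The choice of item may be made elsewhere.** Section 2.10 names no NMQ item or score, and a separate analysis plan may settle it. That is fair as regards the details of analysis. It does not remove the mismatch, because the recall windows, the visits, the identical assessments and the purpose of measuring change are all stated here and do not fit together for the 12-month item.

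**The work-limitation question.** A reader might assume that it shares the fault. Section 2.7 refers it back to symptoms in either window and does not say which applies, so the article alone does not establish that.

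**Conclusion.** The concern holds for the 12-month item. At T1 about 85% of its window, and at T2 about 77%, precede the programme. Recovery in a region with symptoms during those weeks cannot appear as a change from yes to no. The item is very insensitive to benefit, and the switches that do occur are mainly old episodes leaving the window, or recall error.

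The window shares rest only on the stated visit times and on 12 months being 52 weeks. The prevalence figures rest on assumed weekly probabilities and independence across weeks; they show the order of magnitude and are not predictions for this workforce.

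The consequence is limited. The NMQ is one of nine secondary instruments in Table 2. Neither the primary outcome (change in NRS pain from baseline to post-intervention) nor the sample size depends on it. The point should be corrected because the change costs almost nothing, but it does not threaten the study's main result.

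**What to change.** In section 2.7, with a footnote to Table 2:

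1. Use the 12-month item at T0 only, to describe the sample. If the full questionnaire is kept at every visit, state that this item will not be analysed as change.
2. Name the 7-day item as the NMQ change outcome at T0, T1 and T2, for example as each worker's number of symptomatic regions. A count from 0 to 9 also suits the repeated-measures or Friedman analysis in section 2.10.
3. State which recall window the work-limitation question uses. Analyse its change only if that window is short and lies after the programme start at T1 and T2.

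The cost is a sentence or two and a footnote; the 7-day data are already planned. The downside is that a shortened follow-up form departs slightly from the full standard questionnaire, whose Spanish version section 2.7 cites for reliability and content validity. Keeping the full form and leaving the 12-month item out of the change analysis avoids that. The decision is best made before the follow-up forms are used.

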#### Psychosocial and health-related outcomes

2.7.1

*Sleep quality:* Sleep quality will be evaluated using the Pittsburgh Sleep Quality Index (PSQI), a validated self-administered instrument that assesses sleep patterns and disturbances over the previous month across seven components subjective quality, latency, duration, efficiency, disturbances, use of sleep medication, and daytime dysfunction). The PSQI generates a global score ranging from 0 to 21 points, with higher scores indicating poorer sleep quality; a score above 5 is commonly used to identify clinically relevant sleep disturbance (28). The Spanish version of the PSQI has demonstrated adequate reliability and validity in adult populations (29).

*Depression, anxiety and stress:* Symptoms of anxiety, depression, and stress will be measured using the Depression, Anxiety and Stress Scale (DASS-21), providing separate subscale scores (0–42) for each domain. Higher score indicates greater symptoms of severity. Interpretation thresholds for each subscale are normal, mild, moderate, severe, and extremely severe. The MCD is approximately 5–6 points per subscale (30). The DASS-21 has shown good psychometric properties and has been validated in Spanish populations (31).

*Health-related quality of life:* Health-related quality of life will be measured using the EQ-5D-5L a generic questionnaire assessing five dimensions: mobility, self-care, usual activities pain/discomfort, and anxiety/depression, each with five severity levels. It also includes a visual analog scale (VAS) ranging from 0 (“worst imaginable health”) to 100 (“best imaginable health”). Higher score indicates better health status (32). The Spanish version is validated for adult populations (33).

*Work productivity and absenteeism:* Work productivity, activity impairment, and absenteeism will be assessed using the Work Productivity and Activity Impairment questionnaire (WPAI). The instrument provides four outcomes: absenteeism (% of work time missed), presenteeism (% impairment while working), overall work productivity loss, and activity impairment in daily activities outside work. Higher percentages indicate greater impairment (34). The WPAI has been validated in Spanish populations (35).

In addition to clinical and work-related outcomes, selected process indicators will be descriptively reported to contextualize feasibility aspects of the intervention in this occupational setting. These will include recruitment rate, attendance to face-to-face workshops, adherence to the app-based exercise sessions, and retention at follow-up. These indicators will be intended to inform interpretation of the results and guide future-controlled studies.

All outcome variables and their corresponding assessment time points are detailed in Table 2.

**Table 2 tab2:** Outcome measures.

Outcome measure	Baseline (T0)	Post-intervention 8 weeks (T1)	Follow-up 12 weeks (T2)
Primary outcome			
Pain intensity (NRS)	✓	✓	✓
Secondary outcomes			
Musculoskeletal symptoms (NMQ)	✓	✓	✓
Upper-limb muscle strength (Handgrip dynamometry)	✓	✓	✓
Functional capacity (30-s Sit-to-Stand test)	✓	✓	✓
Physical activity level (IPAQ-SF)	✓	✓	✓
Work ability (WAI)	✓	✓	✓
Sleep quality (PSQI)	✓	✓	✓
Depression, anxiety and stress (DASS-21)	✓	✓	✓
Health-related quality of life (EQ-5D-5L)	✓	✓	✓
Work productivity and absenteeism (WPAI)	✓	✓	✓
Sociodemographic and work-related variables	✓	—	—
Process/feasibility indicators			
Recruitment rate	—	✓	—
Workshop attendance	—	✓	—
Adherence to app-based exercise sessions	—	✓	✓
Retention at follow-up	—	—	✓

